### Participant timeline {13}

The participant timeline for treatment and assessments is shown in the table below (Table 3).

**Table 3 Tab3:** Participant timeline

Assessment	All follow-up time points are taken from the date of completion of RT					
	Baseline	Adjuvant RT			3–12 months every 3 months after RT	13–60 months every 6 months after RT
		Week 1	Week 2	Week 3		
Clinical evaluation	X					
Eligibility checklist	X					
Informed consent	X					
Randomization	X					
RT QA	Prior to centre initiation and throughout the trial recruitment period					
RT treatment (control arm)		X	X	X		
RT treatment (test arm)		X				
RT verification (Control Arm)		X	X	X		
RT verification (test arm)		X				
SAE		X	X	X	X	X
Acute toxicity		X	X	X		
FU assessments				X	X	X
EORTC QLQ C30 (control arm)	X			X	At 6, 12 and 18 months after completion of RT	
FACT-B (control arm)	X			X	At 6, 12 and 18 months after completion of RT	
EORTC QLQ C30 (experimental arm)	X	X			At 6, 12 and 18 months after completion of RT	
FACT-B (experimental arm)	X	X			At 6, 12 and 18 months after completion of RT	

Note that patients who undergo sequential tumour bed boost will have their post-radiotherapy assessment postponed till boost is completed. This would mean at the 2nd week in patients receiving 1-week RT and the 4th week in patients undergoing 3-week RT

In each study visit, a clinical assessment including a history and examination will be undertaken. Adverse events related to radiotherapy will be recorded in a case record form. Quality of life questionnaires will be administered on the visits as indicated. During the follow-up period patients will undergo mammogram of intact breast(s) at 12–18-month intervals or as per the institutional policy.

### Sample size {14}

#### Non-inferiority margin and justification for the same

Assuming that the locoregional recurrence rate in the control arm is 5%, a non-inferiority margin of 3% is clinically acceptable and corresponds to a hazard rate of 1.63. The choice of the non-inferiority marginis arbitrary to a significant extent and we base it on the guidance that it should not be larger than the expected benefit from adjuvant radiotherapy. A large volume of data is available regarding the benefit of adjuvant radiotherapy in breast cancer patients. In the setting of breast conservation surgery, the EBCTCG meta-analysis demonstrated that use of adjuvant radiotherapy reduced the 5-year local recurrences by 17% after breast conservation surgery [2], while in the postmastectomy setting the 5-year local recurrence was reduced by 14.7% for N+ patients [3]. The START trials were designed to show a difference of 5% as the non-inferiority margin [28]. This is approximately 33% of the benefit that can be expected from RT vs no RT. Since the START trials have demonstrated that the 40 Gy is non-inferior to 50 Gy we can thus consider a non-inferiority margin of 3% as appropriate for this study.

#### Sample size

The sample is calculated based on the assumption that the 5-year local recurrence rate in the control arm is 5% with an exponential distribution. We hypothesize that the use of 1-week course of adjuvant radiotherapy will not increase the locoregional recurrence beyond 8% (absolute difference of 3%), corresponding to a hazard ratio of 1.63. We further assume that patients will be accrued over 5 years with an initial ramp-up in the first year and that 2% of the patients will be lost to follow-up each year of the trial. The total trial duration is expected to be 10 years to ensure a minimum follow-up of 5 years for the last patient. For a fixed sample size design to achieve the required number of events to achieve a one-sided type I error of 0.025 and a power of 80% the total number of events required is 140. The total planned sample size is 2100 patients.

### Recruitment {15}

Patients will be recruited from the outpatient departments of the disease management group at each institute. No advertising is permitted for recruitment and no inducements will be given for the recruitment of patients in the study. Central randomization will be done at Tata Medical Center using permuted block randomization.

## Assignment of interventions: allocation

### Sequence generation {16a}

Stratified randomization using permuted blocks will be used for randomization. The randomization sequence will be generated using the Robust Randomization App (available at https://clinicalresearch-apps.shinyapps.io/rrapp/) or a similar application and the randomization scheme generated from the app will be then used with the RedCap Randomization module to generate the randomization sequence. Patients will be allocated into the two groups in a 1:1 ratio. The following stratification factors will be used:
Type of surgery: mastectomy or breast conservationRegional nodal radiation: required or notTriple-negative breast cancer: yes or noInstitute

### Concealment mechanism {16b}

Randomization of the patient will be done using the randomization module implemented in the RedCap randomization module in the study database. Central randomization will be done to ensure allocation concealment.

### Implementation {16c}

After screening and eligibility checks are completed, consenting patients will be randomized using the randomization module. The randomization will be done centrally at Tata Medical Center. RedCap provides a data access group feature which ensures that randomization is stratified by the institute. After filling the other stratification factors, the randomize button will be clicked which will then provide the arm allocation information. This information is permanently recorded in the database and cannot be altered in future.

## Assignment of interventions: blinding

### Who will be blinded {17a}

Given the nature of intervention used in the study, no blinding is planned in this study.

### Procedure for unblinding if needed {17b}

As blinding is not being done in this trial, no unblinding will be required.

## Data collection and management

### Plans for assessment and collection of outcomes {18a}

Data related to the trial will be collected and maintained on a RedCap database maintained in Tata Medical Center. The randomization module of RedCap will be used for random allocation into the two arms. Participating institutes will have access to the RedCap data entry system. The RedCap data forms can be printed out and used as such for clinical data entry in the trial if paper form entry is needed. The following forms will be created in Redcap for the data collection purpose:
Demographic informationTrial screening formPretreatment assessmentRadiotherapy plan detailsRadiotherapy plan QA detailsRadiotherapy treatment setup inaccuracy dataRadiotherapy treatment review formFollow-up review formOutcome formQoL capture formSAE reporting form

The RedCap features for longitudinal data collection as well as repeating forms will be utilized for data collection. RedCap also has the facility to set up rules for data quality assurance which will be used to ensure that entered data is of high quality. Planning CT and treatment plan data will be archived in an image bank which is concurrently undergoing development in our institute [29].

### Plans to promote participant retention and complete follow-up {18b}

If a patient or investigator decides to stop the study treatment then the patient’s health status will be periodically reviewed via continued study visits or phone contact, or from their general practitioner or medical records to allow the collection of outcome data. Follow-up assessments including completion of the quality of life questionnaires should still be completed if the patient is willing.

In the event that a patient withdraws from the study entirely, the effective date of the notification will be the date on which their withdrawal is received by the study team. No information about the patient will be collected from that point in time onwards but any information collected prior to that date can be used and forms part of this study.

For patients moving from the area during follow up, every effort should be made for the patient to be followed up at another participating trial centre and for that trial centre to take over responsibility for the patient. A copy of the patient Case Record Forms (CRF) will need to be provided to the new site after appropriate patient consent. Until the new centre agrees (in writing) to take over responsibility, the patient remains the responsibility of the original centre.

### Data management {19}

Access to the data will be available to the principal investigator of the study as well as to the co-investigators after the completion of the study. The DSMC and trial statistician will have access to data while it is ongoing. The data quality and integrity will be checked at quarterly intervals using the data quality checking system available in Redcap. Patient identifiers will be noted as such in the Redcap database and the same will be used for ensuring that any data exports contain de-identified data only. Institutes will have access to the data of their own institute during the trial phase. Once the trial is completed, the main database will be checked for data consistency and quality and then closed for analysis. Additionally, the PI will be asked to sign off key CRFs electronically to ensure completeness and accuracy of the data.

Source documents pertaining to the trial must be maintained by investigational sites. Source documents may include a subject’s medical records, hospital charts, clinic charts, the investigator’s subject study files and the results of diagnostic tests such as X-rays, laboratory tests, and electrocardiograms. The investigator’s copy of the case report forms serves as part of the investigator’s record of a subject’s study-related data. All study-related documentation will be maintained for 10 years following completion of the study or according to existing regulatory requirements.

The following information should be entered into the subject’s medical record:
Subject’s name, contact information and protocol identification.The date that the subject entered the study and the subject number.A statement that informed consent was obtained (including the date).Relevant medical historyDates of all subject visits and results of key trial parameters.Occurrence and status of any adverse events.The date the subject exited the study, and a notation as to whether the subject completed the study or reason for discontinuation

### Confidentiality {27}

The study will be conducted in accordance with applicable rules and regulations. All data generated in this study will remain confidential. All information will be stored securely at the sponsoring institute and will only be available to staff directly involved with the study. For documents transferred between institutions, the data will be securely stored in the RedCap database and access restricted to the trial institute and the CTU through the use of the data access groups features in RedCap.

### Plans for collection, laboratory evaluation and storage of biological specimens for genetic or molecular analysis in this trial/future use {33}

Blood will be collected at the beginning and end of radiotherapy for consenting patients. Ten milligrammes of venous blood will be collected and stored in a Ethylene Diamine Tetraacetate (EDTA) blood tube. The sample will be processed for storing the plasma and buffy coat separately in the biobank. Future studies will be designed to utilize these biospecimens for correlative translational studies investigating fraction sensitivity.

### Interim analyses {21b}

An interim analysis will be planned once 50 patients are accrued in each arm, and in this analysis, we will be evaluating the acute toxicity of the two interventions. The sample size of 50 patients in each arm allows us 80% power to exclude a within-group rate of CTCAE Grade 3 or more acute skin toxicity exceeding 10% (absolute increase) over the target rate of 5% (one-sided type I error of 5%).

The next interim analysis for safety (in terms of locoregional recurrences) will be planned at 3 years when 16 events in total are expected to have occurred. As a result of this interim analysis, the sample size has been increased to 2100 patients (from 2074 without the interim analysis). The critical *Z* value at the time of interim analysis is 3.47 for futility. The following table illustrates the key features of the design (Table 4).

**Table 4 Tab4:** Tabulation of the features of the interim analysis for loco-regional recurrence

Analysis	Value	Efficacy	Futility
**IA1: 11%**	*Z*	3.47	− 1.48
*N*: 1184	*p* (1-sided)	0.0003	0.9318
Events: 16	HR at bound	0.28	3.47
Year: 3	*P* (cross) if HR = 1.63	0.0003	0.07
	*P* (cross) if HR = 1	0.0056	0.008
**Final**	*Z*	1.96	1.96
*N*: 2100	*p* (1-sided)	0.025	0.025
Events: 140	HR at bound	1.17	1.17
Year: 10	*P* (cross) if HR = 1.63	0.025	0.975
	*P* (cross) if HR = 1	0.800	0.200

Asymmetric two-sided group sequential design with binding futility bound, 2 analyses, time-to-event outcome with sample size 2100 and 140 events required, 80% power, 2.5% (1-sided) type I error to detect a hazard ratio of 1 with a null hypothesis hazard ratio of 1.63. Enrollment and total study durations are assumed to be 5 and 10 years, respectively. Efficacy bounds derived using a Lan-DeMets O’Brien-Fleming approximation spending function. Futility bounds derived using a Lan-DeMets O’Brien-Fleming approximation spending function. 1A1 11% = 1st interim analysis done when 11% of the local recurrence events have been observed (information fraction)

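### Acute-toxicity interim: 50 patients per arm give about 76% exact power, not 80%, to exclude a 15% rate of grade 3 or worse skin toxicity at one-sided 5%

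*Protocol article*

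**What the plan says.** Protocol article, Interim analyses {21b}, sets the timing of the look: "An interim analysis will be planned once 50 patients are accrued in each arm". It then justifies that number: "The sample size of 50 patients in each arm allows us 80% power to exclude a within-group rate". The endpoint is a "within-group rate of CTCAE Grade 3 or more acute skin toxicity", so each arm is judged on its own and not against the other. The rate to be excluded is described as one "exceeding 10% (absolute increase) over the target rate of 5" per cent, which is 15%. The stated error is a "one-sided type I error of 5" per cent.

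The section names no test, no event cut-off and no explicit null hypothesis. It attaches no stopping rule to this look.

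**The concern.** To exclude a rate is to reject the hypothesis that the true rate is that high. On this wording the null is a rate of at least 15%, the type I error is clearing an arm whose true rate is 15%, and power is the chance of clearing an arm whose true rate is the 5% target. All the inputs are given, so the 80% can be checked, and on this reading it is not reached.

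The null also matters for how the result is read. A test of 5% against 15% uses the same two rates but limits the chance of flagging an acceptable arm, not the chance of clearing a toxic one. The two tests give different answers at some event counts. At stake is whether the stated power and error rate describe the decision that the sentence says will be made.

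**Working it through.** **Inputs**, all from Interim analyses {21b}: n = 50 per arm; target rate 5%; rate to exclude 5% + 10% = 15%; one-sided α = 5%; stated power 80%. X is the number of patients in one arm with the event, X ~ Binomial(50, p). Expected counts are 50 × 0.05 = 2.5 and 50 × 0.15 = 7.5.

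**1. How close can the stated 80% be reproduced?** No method is named, so I tried the usual ones.
- Exact, null 5% against 15%: P(X ≥ 5 | 5%) = 10.4% is too large and P(X ≥ 6 | 5%) = 3.8% is allowed. Power = P(X ≥ 6 | 15%) = 78.1%.
- Arcsine: h = 2·asin(√0.15) − 2·asin(√0.05) = 0.3444. Power = Φ(h√50 − 1.645) = Φ(2.435 − 1.645) = 78.5%, the same for either null.
- Normal approximation, null 5%: Φ((0.10 − 1.645·√(0.05·0.95/50)) / √(0.15·0.85/50)) = 83.6%.
- Normal approximation, null 15%: Φ((0.10 − 1.645·√(0.15·0.85/50)) / √(0.05·0.95/50)) = 70.9%.

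**2. The literal reading, exactly (null: rate of at least 15%).** Find the largest c with P(X ≤ c | 15%) ≤ 5%. Power is P(X ≤ c | 5%).

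| c of 50 | P(X ≤ c given 15%) | P(X ≤ c given 5%) | one-sided 95% upper limit (Clopper-Pearson) at c events |
|---|---|---|---|
| 2 | 1.4% | 54.1% | 12.1% |
| 3 | 4.6% | 76.0% | 14.8% |
| 4 | 11.2% | 89.6% | 17.4% |
| 5 | 21.9% | 96.2% | 19.9% |

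The rule is at most 3 of 50, with type I error 4.6% and power 76.0%. The next cut-off has ample power but more than double the stated error.

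**3. Is the gap only an effect of whole-number counts?** Let the rule spend exactly 5% by also clearing 4 events with probability (0.0500 − 0.0460)/(0.1121 − 0.0460) = 0.060. Power becomes 0.7604 + 0.060 × (0.8964 − 0.7604) = 76.9%. This randomised rule is the most powerful level-5% test of that null, so 76.9% is a ceiling. The arcsine figure of 78.5% therefore exceeds what any valid 5% test against 15% can achieve here.

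**4. Where the two nulls part.** Against 5%, counts of 0 to 5 are all non-significant. Of these, 0 to 3 exclude 15%. Counts of 4 and 5 do not, since their upper limits are 17.4% and 19.9%.

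**The case against.** The strongest reply is that 80% is a rounded planning figure. The section does not claim an exact calculation, and standard methods on its inputs run from 70.9% to 83.6%. Two of them land within two points of 80%. This stands as far as it goes: a reader who inferred that 80% cannot come from any ordinary method would be wrong, since it is approached when the null is set at 5% or the arcsine formula is used. It does not rescue the sentence as worded, because the first of these tests a different hypothesis and the second overstates the power available against 15%.

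A reader might also infer that the trial will treat a non-significant test against 5% as excluding 15%, so that an arm with a true 15% rate passes 21.9% of the time. The document does not say this. Taken at its word, false clearance is held to at most 5%. Nor would it be right to say that non-significance against 5% never excludes 15%, because 0 to 3 events do.

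The test and cut-off may be given in the full protocol or statistical analysis plan, which are not shown, so their absence from the article is no finding. The point rests only on the power that the article states. It is also fair that this is an early look with no stopping rule attached, with safety overseen by an independent committee.

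**Conclusion.** The concern holds as a small misstatement. For excluding 15% at one-sided 5% with 50 patients per arm, exact power at a true 5% rate is 76.0%, four points below the stated 80%. On the alternative null of 5% the gap is about two points (78.1%), but that test does not deliver the exclusion the sentence describes.

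The result assumes that the rate to exclude is 5% plus 10 points, that power is evaluated at a true rate of 5%, that each arm is assessed alone, and that all 50 patients are evaluable.

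Severity is minor. On the literal reading the error is only that an acceptable arm is somewhat less likely to be cleared than stated; it does not make clearing a 15% arm more likely. The primary analysis, its type I error and the 2100 total are unaffected.

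**What to change.** Rewrite the power sentence in Interim analyses {21b} to say three things:
- the null hypothesis in each arm is a grade 3 or worse acute skin toxicity rate of at least 15%;
- that rate is excluded when the exact one-sided 95% upper confidence limit is below 15%, which with 50 patients means at most 3 events;
- the power at a true rate of 5% is about 76% (type I error 4.6%).

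If a test against 5% was intended, say so, quote 78%, and drop the claim of exclusion.

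The cost is one sentence and a slightly less favourable power figure. Enlarging the look is not proposed: Trial status reports 420 patients randomised by 7 June 2020, so the accrual trigger has passed. If the look has already been made, the report should state which null and cut-off were applied.

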### Objectives {7}

We hypothesize that the locoregional recurrence rate after a 1-week (5 fractions) course of adjuvant radiotherapy will be non-inferior to the standard 3-week course (15 fractions). The primary objective is to compare the cumulative incidence of patients experiencing a locoregional recurrence by 5 years between 1-week and three-week course of radiotherapy. Based on an audit of the outcomes of patients treated at our centre, the cumulative proportion of the locoregional recurrence rate in the control arm is expected to be 5% at 5 years. A non-inferiority margin of 3% would be clinically acceptable in this setting.

The secondary objectives are to compare:
Invasive disease-free survival, defined as the duration of time from randomization to disease recurrence, death due to any cause or any second invasive malignancy at 5 yearsOverall survival defined as the duration of survival from the randomization at 5 years.Rate of CTCAE (version 5.0) grade 3 or more late radiation-related adverse events.The proportion of patients with health-related quality of life (QoL) similar to or better than the baseline at 12 months.

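### The year-3 look is described as a safety analysis, but Table 4 gives it an efficacy bound that would permit a non-inferiority claim before any 5-year data exist

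*Protocol article*

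**What the plan says.** The Interim analyses section introduces the second look by purpose, time and event count: "The next interim analysis for safety (in terms of locoregional recurrences) will be planned at 3 years when 16 events in total are expected". The text then presents 3.47 as the critical Z for futility.

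Table 4 assigns the same number differently. For the first interim (1184 patients, 16 events, year 3), its Efficacy column holds Z 3.47, one-sided p 0.0003, hazard ratio at the bound 0.28, and crossing probabilities of 0.0003 at a hazard ratio of 1.63 and 0.0056 at 1. Its Futility column holds Z −1.48 with a hazard ratio at the bound of 3.47. The footnote calls this an "Asymmetric two-sided group sequential design with binding futility bound, 2 analyses", with null hazard ratio 1.63 and alternative 1, and names a Lan-DeMets O'Brien-Fleming approximation for both bounds.

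The primary objective (Objectives {7}) is "to compare the cumulative incidence of patients experiencing a locoregional recurrence by 5 years between 1-week and three-week course of radiotherapy". On duration, the Sample size section says: "The total trial duration is expected to be 10 years to ensure a minimum follow-up of 5 years for the last patient".

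**The concern.** The text describes a look that can react only to harm or futility. The table describes one that can also succeed. Because the null is a hazard ratio of 1.63, crossing the efficacy bound rejects inferiority by the margin, which is the trial's positive conclusion. Nothing in the article says that the bound is not to be acted on, or that the claim waits for 5-year data.

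Two things are at stake. First, a monitoring committee cannot tell from the article what Z = 3.47 means. The number appears twice in Table 4, as the efficacy Z and as the futility hazard ratio, and the sentence in the text matches neither use. Second, a claim at year 3 would rest on recurrences in the first three years at most, while the objective is framed at 5 years.

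**Working it through.** **Inputs (Sample size section, Table 4 and its footnote).** Control rate: "the 5-year local recurrence rate in the control arm is 5% with an exponential distribution". Margin: "will not increase the locoregional recurrence beyond 8% (absolute difference of 3%), corresponding to a hazard ratio of 1.63". Error rates and events: "one-sided type I error of 0.025 and a power of 80% the total number of events required is 140". Interim: 16 events and 1184 of 2100 patients at year 3.

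**1. The plan's event count.** Freedman's formula gives 137 events at a hazard ratio of 1.63, or 139 with the unrounded ln(0.92)/ln(0.95) = 1.6256. Schoenfeld's gives 132 to 133. The stated 140 is reproduced to within 3%.

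**2. The printed bounds.** Hazard ratio at bound = 1.63 × exp(−2Z/√events).
- Interim efficacy: 1.63 × exp(−2 × 3.47/4) = 0.288 (0.281 with 15.6 events; printed 0.28).
- Interim futility: 1.63 × exp(2 × 1.48/4) = 3.42 (3.45 with 15.6 events; printed 3.47).
- Final: 1.63 × exp(−2 × 1.96/√140) = 1.17 (printed 1.17).

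So Z 3.47 is the efficacy value and Z −1.48 the futility value, as in the table and not as in the text.

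**3. Chance of crossing the efficacy bound.** Drift at a hazard ratio of 1 is ln(1.63) × √(16/4) = 0.977.
- At 1.63: 1 − Φ(3.47) = 0.00026 (printed 0.0003).
- At 1: 1 − Φ(3.47 − 0.977) = 0.0063 (0.0061 with 15.5 events; printed 0.0056).

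In counts, crossing needs a split of about 3 against 13 in favour of the 1-week arm. The nominal 95% interval at the bound is 0.28 × exp(±1.96 × 0.5) = 0.11 to 0.75.

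**4. Follow-up at year 3.** Table 4 leaves 2100 − 1184 = 916 patients for years 4 and 5, or 458 a year. Assuming the same rate in years 2 and 3, the first year contributes 1184 − 916 = 268. With uniform entry within each year:
- Person-years = 268 × 2.5 + 458 × 1.5 + 458 × 0.5 = 1586.
- Mean follow-up = 1586/1184 = 1.34 years.
- Share with 2 years or more = 268/1184 = 23%.
- Expected events at hazard −ln(0.95)/5 = 0.01026 are about 1586 × 0.01026 = 16, agreeing with Table 4.

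If first-year accrual is half the later rate and 2% a year are lost, the mean is 1.30 years and the share 20%. In every case the maximum is 3 years, so no 5-year incidence can be estimated from the data.

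**5. Spending function.** Information fraction: 0.11 as printed, or 16/140 = 0.114.
- Lan-DeMets O'Brien-Fleming, one-sided 0.025: spends about 1e-11 to 3e-11, so Z is about 6.5 to 6.7 and the hazard ratio at the bound about 0.06.
- Hwang-Shih-DeCani, γ = −4: 0.025 × (exp(4t) − 1)/(exp(4) − 1) = 0.00026 to 0.00027, so Z is 3.46 to 3.47, as printed.
- Futility (printed crossing probability 0.008 at a hazard ratio of 1): the named function spends 0.0001 to 0.00015, whereas Hwang-Shih-DeCani with γ = −2 and β = 0.20 spends 0.0077 to 0.0080.

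**6. Effect of removing the interim efficacy bound.** Bivariate normal, correlation √(16/140), futility −1.48, final Z 1.96, 140 events:

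| | With bound | Without |
|---|---|---|
| One-sided type I error | 0.0250 | 0.0248 |
| Power at hazard ratio 1 | 82.06% | 82.05% |

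Power exceeds 80% because this is the Schoenfeld scale, where 132 events suffice. Only the difference between the columns matters here.

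**The case against.** The strongest reply is that no sentence tells anyone to stop or to declare non-inferiority at year 3. The text speaks of safety and futility, the footnote attaches the word binding only to the futility bound, and the trial is planned for 10 years with primary events maturing in April 2029. What follows a crossing may be set out in the analysis plan or a committee charter, neither of which is shown. A stringent early efficacy bound is also an ordinary group-sequential feature. A result that crossed it would exclude a hazard ratio of 1 as well as 1.63, and the chance of that is well under 1%.

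Much of this stands, and it rules out two stronger readings. A reader might infer that the trial would end at year 3 with late toxicity and 5-year survival unobserved. The article does not say that follow-up ceases, and the Participant timeline schedules visits to 60 months, so 5-year estimates could still be obtained later. A reader might also infer that an early claim would be statistically invalid. The confirmatory criterion is the Cox hazard ratio against 1.63 and the design assumes exponential recurrence, so a test at 16 events is valid if hazards are proportional.

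The reply does not remove the contradiction between text and table, or the mismatch with the named spending function. If that function governed, the bound would be near Z 6.5 and could hardly be crossed. That is a further reason to settle which version is in force.

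**Conclusion.** The point holds as an inconsistency with a small but avoidable design consequence. Table 4 and its footnote give a look described as a safety analysis an efficacy bound. Crossing it would permit the main claim on 16 events, with mean follow-up of about 1.3 years and none beyond 3. The text mislabels the value of Z, and the footnote names a spending function that does not produce the printed bounds.

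The expected impact is limited: the chance of crossing is 0.0003 at a hazard ratio of 1.63 and about 0.006 at 1, and type I error is controlled either way. What a year-3 crossing could not deliver at that date is the 5-year incidence, and data that early give little means of checking the proportional-hazards assumption on which the claim would rest.

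The follow-up figures assume uniform entry within years and level accrual after the first. The crossing probabilities use the normal approximation. The Hwang-Shih-DeCani match is an inference from the printed numbers, not something the article states.

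**What to change.** - Remove all five interim efficacy entries from Table 4 (Z, p, hazard ratio, two crossing probabilities) and the matching footnote wording on a two-sided design and derived efficacy bounds. The year-3 look can then cross only the harm/futility bound at Z −1.48.
- Correct the sentence that gives 3.47 as the futility Z.
- Name the spending function that generated the retained bound. The printed values fit Hwang-Shih-DeCani, with γ = −2 for futility; the design output should confirm this.
- State that non-inferiority is concluded only at the final analysis.

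Keep 140 events, 2100 patients and final Z 1.96. Type I error stays at or below 0.025: it is 0.0248 with the futility bound followed, and 0.025 if that bound is overruled, since only the final test at 1.96 could then succeed. Power is unchanged to within 0.02 percentage points. The cost is an edit to one table, its footnote and a few sentences. All that is given up is about a 0.6% chance, at a hazard ratio of 1, of a very early claim.

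### The text labels Z = 3.47 as the interim futility bound, but Table 4 gives 3.47 as the efficacy Z and −1.48 as the futility Z; sentence, table and table note need reconciling

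*Protocol article*

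**What the plan says.** Everything at issue is in the Protocol article, section Interim analyses {21b}, and in Table 4 with its note.

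- Purpose of the look: "The next interim analysis for safety (in terms of locoregional recurrences) will be planned at 3 years when 16 events in total are expected". It is the only interim analysis of recurrence; the other one concerns acute toxicity.
- The sentence: the critical Z "value at the time of interim analysis is 3.47 for futility".
- Table 4, interim row: Z is 3.47 under Efficacy and −1.48 under Futility. The one-sided p row reads "0.0003 0.9318" and the hazard-ratio row reads "HR at bound 0.28 3.47", both in the order efficacy, futility.
- Table 4 note: "Asymmetric two-sided group sequential design with binding futility bound, 2 analyses", with "80% power, 2.5% (1-sided) type I error to detect a hazard ratio of 1 with a null hypothesis hazard ratio of 1.63". The note names the same spending function for both sides; for futility it reads "Futility bounds derived using a Lan-DeMets O’Brien-Fleming approximation spending function".
- Sample size {14}: "the total number of events required is 140".

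**The concern.** The sentence and the table give different futility values on the same scale. The number 3.47 occurs twice in the interim row of Table 4, once as the efficacy Z and once as the hazard ratio at the futility bound, so the labels are easy to cross. The article does not state the sign convention for Z; it has to be inferred from the table.

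This look is described as a safety check on recurrence, so the futility side, where the 1-week arm appears worse, is the one that matters most. It is also the only bound that the prose quotes. The note calls the bound binding, so the design's error rates assume that it is obeyed. A monitoring committee needs one value, with its scale and direction.

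**Working it through.** **Inputs.** Null HR 1.63, alternative HR 1, one-sided 2.5% type I error and 80% power (Table 4 note); 140 final events (Sample size {14}); 16 interim events, labelled 11% information (Table 4), where 0.11 × 140 = 15.4; 1:1 allocation (Sequence generation {16a}).

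**Step 1: does Table 4 agree with itself?** With D events, Z measured against HR 1.63 and positive Z favouring non-inferiority:

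HR at bound = 1.63 × exp(−2Z/√D), and one-sided p = 1 − Φ(Z).

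| Bound | HR, D = 16 | HR, D = 15.4 | Table 4 HR | p computed | Table 4 p |
|---|---|---|---|---|---|
| Interim Z = 3.47 | 0.288 | 0.278 | 0.28 | 0.00026 | 0.0003 |
| Interim Z = −1.48 | 3.42 | 3.47 | 3.47 | 0.931 | 0.9318 |

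The final bound Z = 1.96 with D = 140 gives HR 1.17, as tabulated.

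Crossing probabilities at the interim futility bound:

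- If HR = 1.63: Φ(−1.48) = 0.069 (table 0.07).
- If HR = 1: the drift is ln(1.63) × √16 / 2 = 0.977, and Φ(−1.48 − 0.977) = 0.007 (table 0.008).

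The table is coherent apart from rounding. On its scale Z = 3.47 is an extreme result in favour of the 1-week arm and cannot be a futility bound.

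**Step 2: can the sentence be read, as a Z value, to give the tabulated rule?** With 16 events:

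- Stop if Z ≥ 3.47: stops for futility when the observed HR is 0.29 or less, the wrong direction.
- Stop if Z ≤ 3.47: probability Φ(3.47 − 0.977) = 0.994 when HR = 1.
- Stop if Z ≤ −3.47: needs an observed HR of 1.63 × exp(3.47/2) = 9.24. At a true HR of 2.5 the shift is 2 × (ln 1.63 − ln 2.5) = −0.855, so the stop probability is Φ(−3.47 + 0.855) = 0.0045. The tabulated bound gives Φ(−1.48 + 0.855) = 0.27.

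None of these is the tabulated rule. Read as a hazard ratio, 3.47 matches the futility column exactly.

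**Step 3: do the tabulated bounds match the named spending function?** Lan-DeMets O'Brien-Fleming spending at information fraction t is 2 × [1 − Φ(z/√t)], with z the upper α/2 (or β/2) normal quantile. At t = 16/140 = 0.114:

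- Efficacy, α = 0.025: cumulative spend 3.4 × 10⁻¹¹, so Z = 6.53.
- Futility, β = 0.20: cumulative spend 0.00015, so Z = Φ⁻¹(0.00015) + 0.977 = −2.64, and HR at bound = 1.63 × exp(2.64/2) = 6.1.

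At t = 0.11 the values are 6.66 and −2.73. Table 4 shows 3.47 and −1.48, with 0.0003 of α and 0.008 of β spent, so the note and the table disagree.

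For orientation, Hwang-Shih-DeCani spending with parameters −4 (α) and −2 (β) at 15.4 events spends 0.00026 and 0.0077. It gives Z = 3.47 and −1.46 to −1.49, depending on whether the drift is taken from ln(1.63) or from the 80% power requirement. That is close to the table. It suggests where the figures may come from but does not prove it.

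**The case against.** The strongest reply is that this is a labelling slip beside a complete table. The next sentence sends the reader to Table 4, which gives sign, Z, p, HR and crossing probabilities for both bounds. The futility column itself contains 3.47, as a hazard ratio, so the error may be one word: Z written where HR was meant. On that reading the rule works as tabulated. The monitoring committee is to include an experienced trial statistician, and the statistical analysis plan, not shown here, may hold the operative rule.

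Most of this stands. A reader might infer from Step 2 that the trial would stop almost surely, or that the recurrence safety stop is disabled. The documents do not support either. The first needs a committee to stop for futility unless the observed HR is below about 0.29, with Table 4 in front of it. The second needs a minus sign that the sentence does not have. Nor do the documents show that the committee would act on the sentence in preference to the table.

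The reply does not remove the contradiction. The sentence says Z, the table's futility Z is −1.48, and an unseen plan does not correct a printed figure. The reply also relies on Table 4 as the authority, while the note to that table describes a different pair of bounds.

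**Conclusion.** The sentence misstates the futility bound on the Z scale: 3.47 against a tabulated −1.48. Whether the efficacy Z or the futility HR was carried over cannot be settled from the article; both routes leave the sentence wrong. The defect is in the sentence and not in the tabulated rule, which is usable as printed and coherent across its rows. What is at stake is the clarity of a binding threshold.

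A second inconsistency bears on the correction. The named spending function implies interim Z values of about 6.5 and −2.6, so −1.48 and 3.47 cannot be treated as confirmed until the design output has been checked.

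These results assume 1:1 allocation, the usual log-rank variance of 4/D for the log hazard ratio, and 15.4 to 16 interim events. Moving within that range changes the HR at the futility bound only from 3.47 to 3.42.

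**What to change.** Before the year-3 look:

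1. Retrieve the design output and confirm the interim bounds and the spending function actually used.
2. Rewrite the sentence to agree with it, stating for each bound the scale (Z or HR), the sign and the direction. On Table 4's present figures it would give futility at Z = −1.48 or below (observed HR about 3.47 or more) and efficacy at Z = 3.47 or above (observed HR about 0.28 or less), with positive Z favouring non-inferiority.
3. Correct either the spending function named in the Table 4 note or the tabulated bounds, so that the two agree.
4. Use the same wording in whatever document instructs the monitoring committee.

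If the table is confirmed, the cost is one sentence and one line of the note. If the note is confirmed, the interim bounds and crossing probabilities have to be recomputed and the event and sample-size totals rechecked, which is still a desk exercise.
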